**Methods:**

The Snuggle Bug/ Acurrucadito study is an observational, longitudinal study investigating whether 24-h, actigraphy-assessed, sleep-wake patterns and GM development are associated with RWG among infants in their first year. Based on the Ecological Model of Growth, we propose a novel conceptual framework to incorporate sleep-wake patterns and the GM as metabolic contributors for RWG in the context of maternal-infant interactions, and familial and socio-physical environments. In total, 192 mother-infant pairs will be recruited, and sleep-wake patterns and GM development assessed at 3 and 8 weeks, and 3, 6, 9, and 12 months postpartum. Covariates including maternal and child characteristics, family and environmental factors, feeding practices and dietary intake of infants and mothers, and stool-derived metabolome and exfoliome data will be assessed. The study will apply machine learning techniques combined with logistic time-varying effect models to capture infant growth and aid in elucidating the dynamic associations between study variables and RWG.

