### Power analysis and target population

Using the Hedeker et al. approach [52], for a test of a between groups linear trend difference (comparing normal infant growth to those with RWG), equal sample sizes, 6 time points, a correlation among the repeated measures of 0.5, a compound symmetry structure, a medium effect size of one third of a standard deviation, an α of 0.05, and a power of 0.8, a total sample size of 184 participants (includes for estimated 20% attrition) is needed for Aim 1. To power for Aims 2–3, we reduced all EMG constructs (Fig. 1) into a single virtual covariate to facilitate computation. We then generated simulated data based on a mixed effect logistic regression model that included the virtual covariate, a sleep pattern variable and a GM diversity variable, each randomly drawn from a normal distribution and having six repeated measures. We fixed the effect size of the virtual covariate to be medium (Cohen’s f2 = 0.15), and varied the effect sizes of the sleep pattern variable and the GM diversity variable between medium (f2 = 0.15) and large (f2 = 0.35) as were observed in unpublished preliminary data. Figure 2 shows that 160 infants are required to achieve a power of 0.8 to detect a significant medium-sized effect at α = 0.05. Adjustment for a 20% attrition rate requires that we recruit 192 mother-infant pairs.

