**Fig. 2 Fig2:**
[figure not shown]
Power simulations for Aims 2 and 3. Each point is an average of 100 simulations

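### For Aims 2–3, the target of 192 pairs keeps 160 infants only if attrition is at most 16.7%; the stated 20% would need 200 (a minor arithmetic error)

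*Protocol article*

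**What the plan says.** The section *Power analysis and target population* sizes the study twice.

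- **Aim 1:** a total of 184 participants, described as already including an estimated 20% attrition.
- **Aims 2–3:** a simulation from a mixed effect logistic model with six repeated measures per infant. The effect sizes of the sleep and microbiota variables were varied "between medium (f2 = 0.15) and large (f2 = 0.35) as were observed in unpublished preliminary data". The result read from Figure 2 is that "160 infants are required to achieve a power of 0.8" for a medium effect at α = 0.05. The next sentence is "Adjustment for a 20% attrition rate requires that we recruit 192 mother-infant pairs".

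The larger of the two totals becomes the study size, and the Abstract repeats it: "In total, 192 mother-infant pairs will be recruited". The caption of Figure 2 adds that "Each point is an average of 100 simulations".

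**The concern.** The protocol states a required number (160), a loss rate (20%) and a recruitment target (192), and the third does not follow from the other two. A 20% attrition rate means that 20% of those enrolled are lost. Adding 20% to the number needed at the end is a different operation and always gives a smaller target. The sentence therefore promises protection against more loss than the target can absorb. Because Aims 2–3 set the larger total, the slip sits in the number that determines how many pairs are recruited.

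**Working it through.** **Inputs**, all from *Power analysis and target population* unless noted:

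- required infants for Aims 2–3: 160, at power 0.80 and α = 0.05
- attrition: 20%
- recruitment target: 192, repeated in the Abstract
- simulations per plotted point: 100, from the Figure 2 caption

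The 160 is taken as given. The figure and the full simulation settings are not available, so it cannot be re-derived.

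**1. Reproduce the stated target.** n × (1 + d) = 160 × 1.20 = 192. This matches exactly, and nothing else in the article offers another route from 160 to 192.

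**2. Target that retains 160 after 20% loss.** n / (1 − d) = 160 / 0.80 = 200. Check: 200 × 0.80 = 160. The gap is 200 − 192 = 8 pairs, or 8/192 = 4.2% of the target.

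**3. What 192 leaves after 20% loss.** 192 × 0.80 = 153.6, so about 153 infants with complete follow-up, 6 to 7 fewer than 160.

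**4. Attrition that 192 can absorb.** 1 − 160/192 = 32/192 = 16.7%.

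**5. Approximate effect on power.** Assume exactly 80% power at 160, a two-sided 0.05 test (the article does not state sidedness), and no information from infants who are lost. With the noncentrality scaled by the square root of the sample size:

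power(n) ≈ Φ[(1.960 + 0.842) × √(n/160) − 1.960]

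| n | power |
|---|---|
| 160 | 0.800 |
| 154 | 0.785 |
| 153 | 0.782 |

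The loss is about 1.5 to 2 percentage points.

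**6. Precision of the simulation behind the 160.** With 100 replicates and true power 0.80, the Monte Carlo standard error is √(0.80 × 0.20/100) = 0.04. An approximate 95% range is 0.80 ± 1.96 × 0.04, or 0.72 to 0.88. A difference of 0.02 is half of one standard error.

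**7. Aim 1.** The stated 184 already includes attrition, and 192 exceeds it. The arithmetic above does not touch that figure.

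**The case against.** The strongest reply is that the error makes almost no practical difference. Four points support it.

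- **Simulation noise.** With 100 replicates per point, the simulation cannot tell a power of 0.80 from 0.78. This stands, and it is why the point is minor.
- **Unknown power at 160.** If 160 was simply the first plotted size to pass 0.80, the true power there could be somewhat higher, and 153 might still reach the target. This also stands, because the figure cannot be read.
- **Partial data.** The power model uses repeated measures, so infants lost part-way can contribute the visits they completed. The primary outcome, rapid weight gain, is assessed at 6 months while visits run to 12 months, so an infant lost after the 6-month visit already has it. The article does not say when losses are expected. This stands in part: treating every lost infant as contributing nothing is a worst case. But the simulation was specified with six measures per infant, so partial data would recover only some of the loss, and the article does not use this argument to justify 192.
- **Aim 1 is covered.** As stated, it is.

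None of this rescues the sentence itself. The protocol chose to adjust for 20% attrition, and 192 does not do so.

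A reader might infer that the study is underpowered, or that its sample size fails all its aims. The documents do not support either reading. The shortfall is 8 recruits, the approximate power loss is smaller than the simulation can resolve, and only the Aims 2–3 sentence is affected.

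**Conclusion.** The attrition adjustment for Aims 2–3 is wrong as written. That conclusion needs only the three figures printed in the article: 192 is 160 × 1.2, a 20% loss calls for 200, and 192 keeps 160 infants only up to 16.7% attrition.

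Its importance is minor. The estimated loss of 1.5 to 2 points of power rests on the assumptions set out in step 5 of the working, none of which the article lets a reader confirm. It shows the order of magnitude and is not a substitute for the study's own power figure.

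**What to change.** Change the one sentence in *Power analysis and target population* to say that recruiting 192 pairs retains 160 infants with attrition of up to 16.7%, and note that 20% attrition would correspond to 200 pairs. The total in the Abstract can then stay as it is, and no extra enrolment is needed.

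Do not write a power of about 0.78 into the protocol on the strength of the approximation above. If the authors prefer to keep 20% as the planning rate with 192 recruited, they should rerun their own mixed logistic simulation at about 153 infants and quote that result. More than 100 replicates would be needed to resolve a difference of this size.

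The cost is one sentence and a slightly lower stated attrition allowance, plus one simulation run if a power at the smaller number is wanted.

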**Fig. 2 Fig2:**
[figure not shown]
Power simulations for Aims 2 and 3. Each point is an average of 100 simulations

### Participants and procedures

#### Maternal sample subject eligibility

Inclusion criteria are (1) English- and/or Spanish-speaking mothers in their 3rd trimester of pregnancy through 3 weeks postpartum from the Phoenix, Arizona community; (2) ages 18 to 40 y; (3) with a telephone contact; and (4) not intending to move from the area for at least 1.25 years. Exclusion criteria are (1) mothers who have chronic metabolic diseases (e.g., types 1 and 2 diabetes prior to pregnancy, cardiovascular disease) that impact fetal growth; (2) experienced a high-risk pregnancy (e.g., preeclampsia, HIV infection); (3) delivered a small or large newborn (< 2500 g or > 4000 g); (4) hospitalization after discharge of infant; (5) separation from infant; (6) experiencing significant postpartum complications; (7) report alcohol, tobacco, and marijuana use in the second and/or third trimesters [53]; or (8) report illicit substance use during any trimester.

#### Infant sample subject eligibility

Inclusion criteria include full-term (≥37 weeks of gestation) singleton infants who have no growth abnormality or other endocrine, chromosomal, or genetic abnormality, or severe illness-related comorbidity that could impact growth and development. Exclusion criteria are (1) mother-infant pairs who are not discharged together from the hospital; or (2) infants born with congenital abnormalities or conditions that may be expected to result in developmental delays or birth weights < 2500 g or > 4000 g.

Potential participants will be identified by providers and research staff through in-house recruitment from obstetrics and pediatric units at a local public hospital system, and a network of Supplemental Nutrition Program for Women, Infants, and Children (WIC) clinics. Advertisements will also be distributed through social media, Arizona State University (ASU) Institutional listservs, word-of-mouth, sharing flyers with active study participants, community events, and health professional referrals from clinical and community partners. Eligible participants will provide their contact information. Regular telephone calls, emails, or text messaging contacts will be made to determine birthdate, if eligibility is maintained, and to schedule the first in-home visit. Secondary (e.g., family member, friend) contacts will be obtained in case participants lose phones or change numbers. Enrollment and consent will occur at the first in-home visit at 3-weeks post-delivery.

Study procedures are designed to capture periods during which important neurodevelopmental milestones tend to occur, which have also been associated with early life adiposity [53] (Fig. 3). In-home visits will be conducted in near time to 3 and 8 weeks, and 3, 6, 9, and 12 months postpartum. Along with major neurodevelopmental milestones that tend to occur at these ages, important shifts in infant feeding [54–56], sleep-wake pattern development [57–61], and GM community changes that have previously been associated with infant and childhood weight status [34, 37, 62–64] tend to coincide with these time periods.

**Fig. 3 Fig3:**
[figure not shown]
Flow chart of study procedures

At all home visits, research staff who speak English and Spanish will assess infant anthropometrics, administer brief sleep and health-related questionnaires and explain how to complete a 3-day diet record, instruct the mother on proper retrieval of infant and maternal fecal, infant urine, and maternal breast milk samples, and provide mothers and infants with wrist and ankle actigraphs, respectively, to capture sleep data. After data collection, participants will mail back actigraphs, sleep diaries, and dietary recall forms in pre-stamped boxes. The first participant was enrolled on 09 Nov 2020. Recruitment and follow-up assessments are ongoing.

Procedures were adapted to account for the COVID-19 pandemic such that data collection could be conducted through primarily electronic delivery (e.g., video conferencing, instructional videos, online or telephone survey administration), drop-off and curbside pick-up of research equipment and samples, and/or outdoor or social distanced interactions at participant homes. On the day of the home visit, research staff will take their temperature and complete a COVID-19 symptom self-attestation survey maintained by the study investigators. Participants will also complete a COVID-19 symptom attestation survey for themselves, their infant, and all members of their household prior to the visit. Staff will maintain appropriate social distancing measures while interacting with participants, and use personal protective equipment including masks, gloves, and hand sanitizer. If the mother would prefer for study staff to not have physical contact with the infant, the staff will instruct the mother how to accurately measure their baby under the staff’s supervision. After the visit, the staff will disinfect surfaces that have come into contact with participants (e.g., weight scale) before packing up all study equipment.

### Assessment of RWG and infant growth

RWG is the primary outcome and weight gain over 12 months is a secondary outcome in this study. Infant length and weight will be measured with portable recumbent length boards (nearest mm) and electronic digital scales (nearest 0.1 kg), respectively. Infants will be nude at the time of weighing and will be measured recumbent to maintain measurement consistency. Weight measures will be recorded on the weight-for-age (W/A) percentile growth grid from the National Center for Health Statistics [65] to determine body mass in children under 2 years of age. W/A percentiles will be converted to Z-scores to allow group comparison by sex. Infant head circumference will be measured to the nearest mm using a flexible tape measure (Hopkins Medical Products) designed for infant heads. Infant waist circumference will be measured to the nearest mm using a Gulick II tape measure with tension spring.

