## Background

### Early rapid weight gain in infancy contributes to childhood obesity

Early childhood obesity is a serious health problem. In 2019, 38.2 million U.S. children less than 5 years old were overweight or obese, with greater prevalence among low- and middle-income families [1]. Of those under 2 years, 8.1% had high weight-for-recumbent length (i.e., at or above the 95th percentile) [2]. Further, obese children are more likely to become obese adults [3]. Rapid weight gain (RWG) in the first 6 months of infancy, defined as a greater than 0.67 positive change in weight-for-age Z-score (difference between centile lines on standard growth charts) [4], is associated with greater total weight gain from 0 to 12 months and greater weight-for-length and weight-for-age percentiles at 36 months [5]. It also increases the odds of obesity across the life course [6–9] and relates to adverse health outcomes later in life, including hypertension, diabetes, and cardiovascular diseases [10]. Further, RWG in the first 3 months is more predictive of poor cardiometabolic outcomes than any other 3-month period in the first year of life [11]. Despite robust, globally diverse cohort data accounting for numerous confounding factors present from conception to birth on childhood obesity, few studies have focused on RWG determinants and timing in the birth-to-6-month period.

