### Assessment of covariates

Covariates from each EMG construct (Fig. 1) will include child characteristics, maternal/family characteristics and context, feeding practices and dietary intake of infants and mothers, and home and care environmental factors/exposures. Interactions among EMG constructs also will be assessed, including maternal-child interactions and feeding interactions. An overview of the measures and their relation to ecological constructs are provided in Table 1.

**Table 1 Tab1:** Summary of study variables and measures, by Ecological Model of Growth construct

			Prepartum	Postpartum					
Ecological Construct	**Variable/Type**	**Measures/Instruments**	**Pregnancy (3rd trimester)**	**3 wk.**	**8 wk.**	**3 mo.**	**6 mo.**	**9 mo.**	**12 Mo.**
Child (Host/Agent)	Birth History	Gestational age, method of delivery, birth weight & length, day 2–5 weight & length, duration of labor, antibiotic exposure (from medical chart & reported)		✓					
	Child demographics	Sex, race/ethnicity		✓					
	Medical History	Antibiotic use, illnesses, other medications		✓	✓	✓	✓	✓	✓
	Infant Temperament	Infant Behavior Questionnaire – very short form					✓		
	Reported Sleep	Brief Infant Sleep Questionnaire and parent-reported sleep diaries (5 days each		✓	✓	✓	✓	✓	✓
	Objective Sleep	Ankle actigraphy (5 days each)		✓	✓	✓	✓	✓	✓
	Food Allergy	FDA and CDC Infant Feeding Practices study II						✓	
	Gut microbiome and metabolomics	Soiled diaper & swabs (Microbial genomic DNA and metabolites)		✓	✓	✓	✓	✓	✓
	Intestinal cell transcriptomics (exfoliomics)	Soiled diaper (Microbial genomic RNA and human intestinal cell RNA)		✓	✓	✓	✓	✓	✓
	Exposure to nutrients, environmental phenols, and phthalates *	Urine sample with urine collection bag		✓	✓	✓	✓	✓	✓
	Anthropometrics	Weight and length on standardized instruments		✓	✓	✓	✓	✓	✓
Maternal & Family	Maternal demographics	Age, education, race/ethnicity, income, nativity, length of time in U.S., occupational status, shift work status, parity, birth spacing,	✓	✓					
	Maternal pregnancy factors	Pre-pregnancy body mass index, gestational weight gain, complications, medication, antibiotic exposure, alcohol/tobacco exposure (from medical chart & reported)	✓	✓					
	Acculturation	Brief Acculturation Rating Scale for Mexican Americans		✓					
	Employment changes	Return to work timing, shift work status			✓	✓	✓	✓	✓
	Discrimination	Everyday Discrimination Scale			✓				

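### Rapid weight gain (RWG) is derived from weights to 0.1 kg by way of a percentile grid, which loses a little avoidable information at the 0.67 cut-off

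*Protocol article*

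**What the plan says.** All references are to the protocol article.

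- **Outcome** (Assessment of RWG and infant growth): "RWG is the primary outcome and weight gain over 12 months is a secondary outcome in this study".
- **Cut-off** (Background, on early rapid weight gain): RWG in the first 6 months is "defined as a greater than 0.67 positive change in weight-for-age Z-score (difference between centile lines on standard growth charts").
- **Measurement** (Assessment of RWG and infant growth): weight is taken with "electronic digital scales (nearest 0.1 kg"). Length, head and waist are taken to the nearest mm.
- **Derivation** (same section): "Weight measures will be recorded on the weight-for-age (W/A) percentile growth grid from the National Center for Health Statistics", and then "W/A percentiles will be converted to Z-scores to allow group comparison by sex". Percentiles are therefore the stated source of the Z-scores.
- **Birth weight**: infants with "birth weights < 2500 g or > 4000 g" are excluded. Table 1 lists "Gestational age, method of delivery, birth weight & length" under birth history, from chart and report. The covariate text calls the birth data mother-reported. Neither source is the study scale.

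The article does not say whether percentiles are read by eye or computed, to what precision, or what happens to a weight beyond the outer line. It states no cap.

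**The concern.** The primary outcome is a yes/no call on whether a difference of two Z-scores exceeds 0.67. Each lossy step before that comparison can flip infants close to the cut-off. Rounding to 0.1 kg is one such step. Passing through percentiles is a second, if they are read coarsely: in the upper tail one whole percentile spans a large step in Z (97th = 1.88, 98th = 2.05, 99th = 2.33). Heavy newborns need a 6-month Z in that region to count as RWG.

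At stake is some noise in the primary outcome, which would weaken associations of sleep and gut microbiota with RWG slightly. If readings were also capped, true RWG among infants with high birth weight would be missed in one direction only.

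**Working it through.** **1. The plan's own figure.** z(0.75) − z(0.50) = 0.6745, so 0.67 reproduces as the gap between adjacent centile lines (50th to 75th). The cut-off itself is sound.

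**2. Inputs.** From the article: resolution 0.1 kg, cut-off 0.67, eligible birth weight 2.5–4.0 kg, and 160 analysable infants (power section), used only to scale counts. Assumed, not in the article: birth weight mean 3.4 kg and SD 0.47 kg; 6-month SD 0.87 kg; birth to 6-month Z correlation ρ of 0.3–0.5. Variants: birth mean 3.2–3.5 kg with SD 0.45–0.5 kg, and 6-month SD 0.85–0.9 kg.

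**3. Rounding error in Z** = 0.05/SD at most; root mean square = (0.1/√12)/SD = 0.029/SD.

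| Weight | Maximum | Root mean square |
|---|---|---|
| 6 months, SD 0.87 kg | 0.057 | 0.033 |
| Baseline, SD 0.47 kg | 0.106 | 0.061 |

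**4. Misclassification by hand.** The share flipped is about the density of the true change at 0.67 times the mean absolute error.

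- SD of the change = √(2(1−ρ)) = 1.18 (ρ = 0.3) or 1.00 (ρ = 0.5). Density at 0.67 = 0.288 or 0.319.
- 6-month weight rounded only: mean absolute error 0.057/2 = 0.029, so 0.288 × 0.029 = 0.8% to 0.319 × 0.029 = 0.9%.
- Both rounded: mean absolute error 0.106/2 + 0.057²/(6 × 0.106) = 0.058, so 1.7% to 1.9%.

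This ignores the cut on birth weight, which narrows the distribution slightly.

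**5. Simulation** with birth weight cut at 2.5–4.0 kg; true RWG share 26–30% under the main assumptions.

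| Scenario | Infants misclassified |
|---|---|
| 6-month weight rounded, birth weight in grams | 0.9–1.0% (about 1.5 of 160) |
| Both weights rounded to 0.1 kg | 1.8–2.0%; up to 2.2% in the variants (about 3 to 3.5 of 160) |
| Whole-percentile reading only, no rounding | 0.4–0.6% (under 1 of 160) |
| 6-month weight rounded, whole percentiles, cap at 99th, 97th or 95th | about 1–1.7% |

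With whole percentiles and a 97th or 95th cap, about 2–5% of true RWG cases are missed in total, rounding included. With 42 to 48 cases among 160 (0.26 × 160 to 0.30 × 160), that is about 1 to 2 infants.

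**6. Ceiling, if a cap existed.** The highest birth Z that can still become RWG is z(c) − 0.67: 1.645 − 0.67 = 0.975 for the 95th centile, 1.881 − 0.67 = 1.21 for the 97th. A 4.0 kg newborn has Z = (4.0 − 3.4)/0.47 = 1.28 (1.0–1.8 across the variants) and needs 1.28 + 0.67 = 1.95 at 6 months (1.7–2.45). Across the variants, 0.7–14% of eligible infants lie above the 95th-centile limit and 0–8% above the 97th. Most of these would not be RWG anyway: true cases lost to the ceiling are 0.2–4% and 0–2%. With no cap, none are lost.

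**7. Effect on associations.** With only the 6-month weight rounded, about 1.6–1.8% of cases are missed and 0.6–0.7% of non-cases are called RWG. If the error does not depend on exposure, a risk difference shrinks by a factor of about 1 − 0.018 − 0.006 = 0.976, or 2–3%.

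**The case against.** The strongest reply is that the point is small and that its alarming versions are not in the document.

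- **Ceiling.** A reader might infer that the heaviest eligible newborns cannot be classed as RWG. That needs readings that stop at a top line, and the article states no cap, no outer line and no reading precision. A percentile carried with enough decimals maps one-to-one to Z and loses nothing. Off-chart handling is also the kind of detail a condensed article leaves to the full protocol. This objection stands: the ceiling is only a conditional risk.
- **Both weights rounded.** If the baseline is birth weight, it comes from chart or mother and not from the 0.1 kg scale. This stands too. The 2% figure applies only if the baseline is a study weight; otherwise the figure is about 1%.
- **Snapping to printed lines.** If each weight were moved to the nearest printed line, about 9–11% of infants would be misclassified. The article does not say this is done, so the figure does not describe this plan.
- **Scale resolution.** 0.1 kg may be the instrument's limit. The recording part of the remedy then falls away, but the direct calculation of Z does not.

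The stated route itself remains: weight to 0.1 kg, grid, percentile, then Z. It is the derivation that the article fixes for the primary outcome, and it can only match or do worse than computing Z directly.

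**Conclusion.** The point holds as a free improvement to a stated method and not as a threat to the study. About 1% of infants (1 to 2 of 160) would be misclassified by rounding the 6-month weight, and about 2% if the baseline is also a study weight rounded to 0.1 kg. Whole-percentile reading with a 97th or 95th cap would bring missed RWG to about 2–5% of cases in total, but neither is stated. All sizes rest on assumed weight means, SDs and correlations that the article does not give; within the ranges tried, the conclusion does not change. The documents do not support saying that heavy newborns are barred from RWG, or that the associations would be materially weakened.

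**What to change.** - Compute weight-for-age Z directly from weight, sex and exact age with the LMS parameters of the chosen reference. Apply the 0.67 cut-off to these unrounded Z-scores and use percentiles for display only. This also removes any question of how values beyond the outer lines are read.
- Record weight at the scale's full display resolution where that is finer than 0.1 kg.
- For infants already enrolled, recompute Z from the stored weights. Enrolment began in November 2020 and follow-up is ongoing, so the resolution is worth settling promptly: digits that were never recorded cannot be recovered.

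**Cost:** a standard calculation and, where the scale allows, one more decimal on the form. No new measurements or visits are needed.
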